#### 3.7.4. Secondary Endpoints for Effectiveness

The analysis of the secondary effectiveness endpoints will be performed with the same type of mixed regression model as described for the primary endpoint.

Overall survival (OS) is defined as the time from randomization until death from any cause, or as time from randomization until the patient was last alive (censored observations).

The OS rate will be estimated and described using the Kaplan-Meier method. Further analyses incorporating relevant prognostic factors will be conducted with Cox proportional hazards regression models.

Cause-specific survival will be defined as time from randomization until death from a specified cause (sudden death; 3-point MACE (a composite of cardiovascular death, non-fatal stroke, or non-fatal myocardial infarction)). Patients who are alive will be considered as censored observations and death from other causes will be considered as a competing event. The estimation of cumulative incidence rates will be applied in order to account for the presence of competing events. 

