## 2. Experimental Design and Methods

### 2.1. Study Design

DiaTT will be an interventional, cluster randomized (1:1), multicenter, controlled trial. After screening of dialysis centers and patient recruitment, 28 centers will be cluster randomized to IG or UC, as depicted in Figure 1. The randomization of centers will be stopped once a minimum of n = 1100 patients have been recruited. The intervention will consist of 12 months’ combined exercise training (aerobic and resistance), initiated after the baseline visit (V1), compared to UC without intervention.

The primary endpoint will be a change in the Sit-to-Stand (STS60) test result [15] from baseline to 12 months between groups. Secondary endpoints will include physical functioning (Timed-Up-and-Go test (TUG)), the Six-Minute Walk test (6MWT), the Grip Strength Test (GST)), frailty (Multidimensional Prognostic Index (MPI)), quality of life (SF-36), 3-point Major Adverse Cardiovascular Events (MACE), hospitalizations, overall survival, quality of HD (measured as serum phosphate and other laboratory values), medication (phosphate binders, erythropoietin), health literacy (HLS-EU-Q16 Health Literacy Questionnaire) and health economics (total costs of medication, hospitalization, therapeutic remedies, transportation, medical assistance tools, nursing care and sick leave from workplace). 

The study has been registered at ClinicalTrials.gov NCT03885102.

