### 3.4. Adverse Events and Serious Adverse Events 

The following adverse events (AE), potentially linked to intradialytic exercise, will be recorded throughout the study: venous needle displacement or catheter disconnection during HD symptomatic hypotension during HD (clinically symptomatic, requiring medical intervention) and episodes of cramping (calves) during HD (requiring medical intervention). 

The following serious adverse events (SAE) will be recorded on the eCRF regardless of their occurrence during or between HD sessions: hospitalization (admission or discharge diagnosis) and death, including date and cause of death.

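### Section 3.7.4 contradicts itself on 3-point MACE: the composite includes non-fatal stroke and infarction, but the event and censoring rules recognise only deaths

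*Protocol article*

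**What the plan says.** Three statements in section 3.7.4 of the protocol article, one after the other, set up the analysis.

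- The event: "Cause-specific survival will be defined as time from randomization until death from a specified cause".
- The causes, given in brackets: sudden death, and "3-point MACE (a composite of cardiovascular death, non-fatal stroke, or non-fatal myocardial infarction".
- The handling of everyone else: "Patients who are alive will be considered as censored observations and death from other causes will be considered as a competing event".

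The estimator follows: "The estimation of cumulative incidence rates will be applied in order to account for the presence of competing events".

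Section 2.1 names MACE in the list of secondary endpoints, as an item distinct from survival: "3-point Major Adverse Cardiovascular Events (MACE), hospitalizations, overall survival". It gives no components and no event rule. The only definition in the article is the one in section 3.7.4.

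**The concern.** A non-fatal stroke or infarction cannot be a cause of death, and a patient who survives one is alive and so censored under the stated rule. The definition of the composite and the rules for analysing it therefore conflict within one paragraph. An analyst who follows the event and censoring rules would report cardiovascular death under the name of 3-point MACE. An analyst who follows the definition would have to invent the event time, the censoring rule and the handling of a death that comes after a non-fatal event.

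At stake are the event count, the cumulative incidence and the meaning of any group comparison for a named secondary endpoint. The introduction says that morbidity and mortality are investigated to support reimbursement of intradialytic exercise, so readers will look at this result. An event rule left open could also be settled late, once data have accrued.

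**Working it through.** The article states no MACE rate, event count, hazard ratio or power, so it has no figure to reproduce. The check applies the rules of section 3.7.4 literally to each type of patient course over 12 months and compares the result with a time-to-first-component rule. The months are illustrative.

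**Literal rule.** Cardiovascular death is an event at death. Any other death is a competing event at death. Alive at month 12 is censored.

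**Time-to-first-component rule.** The first of cardiovascular death, non-fatal stroke or non-fatal infarction is the event. Non-cardiovascular death before any of these is the competing event. Alive and free of all three is censored.

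| Course | Literal rule | First-component rule |
|---|---|---|
| Non-fatal infarction month 4, alive month 12 | censored, 12 | event, 4 |
| Non-fatal stroke month 3, non-cardiovascular death month 9 | competing event, 9 | event, 3 |
| Non-fatal infarction month 5, cardiovascular death month 10 | event, 10 | event, 5 |
| Cardiovascular death month 6 | event, 6 | event, 6 |
| Non-cardiovascular death month 7 | competing event, 7 | competing event, 7 |
| Alive, no event | censored, 12 | censored, 12 |

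The two rules differ in exactly the three courses that contain a non-fatal component. In the first two the event is lost; in the third it is delayed by 5 months. Under the literal rule, what remains is time to cardiovascular death.

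**Does another part of the article supply a different rule?** Section 3.7.4 opens with a general statement: "The analysis of the secondary effectiveness endpoints will be performed with the same type of mixed regression model as described for the primary endpoint". That model is a linear mixed model for repeated STS60 values. It defines neither a MACE event nor a censoring time. Section 2.1 only names the endpoint. No other section gives an event rule for MACE.

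**Illustration of size, all rates assumed.** Take 1100 patients (section 3.7.1), a 12-month MACE risk of 8% to 16%, and a non-fatal share of first events of 30% to 70%.

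- Composite events: 1100 × 0.08 = 88, up to 1100 × 0.16 = 176.
- First events not counted at 8% risk: 88 × 0.30 ≈ 26 to 88 × 0.70 ≈ 62.
- First events not counted at 16% risk: 176 × 0.30 ≈ 53 to 176 × 0.70 ≈ 123.

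For each pair of assumptions the result is an upper bound, because it supposes that no patient with a non-fatal first event later dies of a cardiovascular cause during follow-up. Such patients would still be counted, only later.

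**What is untouched.** The sample size in section 3.7.1 rests on STS60 alone: the design factor is 1 + 49 × 0.05 = 3.45, and 260 × 3.45 = 897. No MACE input enters it.

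**The case against.** The strongest defence is that the intent is easy to guess. The bracket names the non-fatal components as part of the endpoint, so the authors probably meant a time-to-first-MACE analysis and merged two definitions in one sentence. That is plausible, and it limits how far the criticism can go. A reader might infer that the trial will certainly ignore non-fatal events. The article does not support this: it states two incompatible things and does not say which prevails. The loss of non-fatal events is a consequence of the literal reading only.

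Guessing the intent does not repair the text, however. Reading the word for death in the first sentence as event would still leave the second sentence censoring everyone alive.

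A second defence is that a journal article condenses, and that section 3.7 promises a detailed SAP, to be completed before database lock. That would answer an omission. Here the article states an event rule and a censoring rule, and they do not fit the endpoint. The coming SAP does mean that the correction can be made without touching the design.

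Three further limits stand:

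- Section 2.1 cannot be cited as a second, contradicted definition. It shows only that MACE is an endpoint in its own right.
- The article attaches no power, alpha or decision rule to MACE, so this is not a defect that threatens the trial's main conclusion.
- Section 3.4 lists, as serious adverse events, "hospitalization (admission or discharge diagnosis) and death, including date and cause of death". It does not say that MACE is derived from these records, and it states no date for a hospitalization or non-fatal event. Equally, nothing there shows that the needed data are missing.

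**Conclusion.** The point holds as an internal contradiction in section 3.7.4 and should be fixed. Followed literally, the event and censoring rules turn 3-point MACE into time to cardiovascular death. This conclusion rests on the wording alone and needs no assumed rate.

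The number of events affected cannot be stated from the article. The range worked above only shows that the count could be material under assumed rates, and each figure in it is an upper bound. The effect is confined to one secondary endpoint. It would be going too far to say that the trial's results as a whole, its primary analysis or its sample size are compromised.

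**What to change.** Split the paragraph in section 3.7.4 into two definitions and carry them into the SAP before the blind review.

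1. **Cause-specific survival:** keep this for fatal causes, here sudden death, with death from other causes as the competing event and living patients censored. No additional cause-specific endpoint is needed.
2. **3-point MACE:** time from randomization to the first of cardiovascular death, non-fatal stroke or non-fatal myocardial infarction. Non-cardiovascular death before a first MACE is the competing event. Only patients alive and MACE-free at last follow-up are censored, at that time. The cumulative incidence estimator already planned can stay.

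The cost is about one paragraph of wording. Non-fatal events could probably be identified from the hospitalization diagnoses recorded under section 3.4. The sponsor should confirm that these records carry a usable event date and state that MACE will be derived from them.

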#### 3.7.5. Health Economics 

The health economic data will be analyzed descriptively and compared between the treatment groups using the FAS (i.e., medication (total costs), hospitalization (days in hospital, total costs), therapeutic remedies (total costs), transportation (total costs), medical assistance tools (total costs), nursing (total costs) and sick leave from the work-place (days)).

Additional health insurance data will be collected from patients insured with one of the participating health insurance companies. In order to assess whether the study population differs from typical German HD patients, basic characteristics will be compared, i.e., age, sex, nursing, comorbidities. 

## 4. Expected Results/Discussion

The DiaTT-trial will be the largest cluster randomized, controlled interventional trial for intradialytic exercise combining endurance and resistance exercise to date. It will address a need that is highly prevalent in many dialysis units and matters greatly to patients [18]. After the initiation of HD, many patients suffer from a pronounced, sustained decline in physical functioning, independent of sex, age, race or previous physical functioning (n = 3702 nursing home residents starting HD, activities of daily living +2.8 points, CI 2.5–3.0) [19]. The same is true for patients returning to ambulatory dialysis after prolonged hospitalizations. Without any treatment or intervention, 50% of CKD patients undergoing HD report a sedentary lifestyle, with exercise taken less than once a week [4] and a high proportion of frailty [3]. Frailty itself is associated with increased short-term (≤3 years, HR 2.18, 95% CI 1.76–2.70) and overall mortality (≥3 years, HR 1.71, 95% CI 1.20–2.44) in these CKD patients when compared to CKD patients without HD (meta-analysis including 12 cohort studies, n = 127037 patients with CKD, 2007–2019) [20]. Long hours without physical activity during HD, together with uremia-induced impaired neuromuscular functioning, low cardiorespiratory fitness and a high prevalence of disability and multi-morbidity [17] result in a progressive decline in physical functioning that is associated with low quality of life and high morbidity and mortality [1].This may be counteracted by active rehabilitation programs and exercise, as has been highlighted by several meta-analyses and reviews [3,5,6,21,22,23,24,25,26]. In particular, intradialytic exercise has been shown to improve physical functioning and cardio-pulmonary exercise capacity (peak oxygen consumption), as reported by Sheng et al. in 2014 (24 RCTs including n = 997 CKD patients on HD) [21] and Ferrari et al. in 2020 (50 RCTs; n = 1757 CKD patients on HD) [5]. 

### 4.1. Intervention Program

The optimal dose of intradialytic training has not been determined. However, intradialytic cycling alone (13 RCTs, n = 369 CKD patients on HD) shows equivocal results [27], whereas combinations of resistance training and aerobic exercise were found to be better at improving physical functioning than either resistance or aerobic exercise training alone [6,8,12], which is in line with the results of our pilot study [9]. Using a combined resistance and aerobic exercise training program has produced very good results, even for very sick patients, and it has demonstrated high long-term adherence rates [9]. Since there is evidence for better outcomes with higher frequency and longer duration of exercise [8,9,28], the targeted training frequency will be thrice-weekly for 12 months in this trial.

### 4.2. Clinical Endpoints

The choice of increased sit-to-stand repetitions in 60 s (STS60 test) as the primary endpoint is based on studies that indicate that it is a reliable parameter for the quantification of relevant changes in physical functioning in CKD patients [15]. The Six-Minute Walk Test (6MWT), the Timed-Up-and-Go (TUG) test and the Grip Strength Test (GST) have been shown to reflect the activities of daily living [6,8,29,30,31].

Improvement in quality of life is an important effect of exercise that is a high priority for patients treated with HD, which has been shown consistently in most trials of exercise interventions [32]. Assessing patients’ quality of life with the SF-36 instrument will therefore be an important secondary endpoint [33]. 

### 4.3. Safety

Exercise training during HD is generally considered safe if general precautions are followed [22,26]. This includes patients with a wide range of disabilities and comorbidities. Therefore, in DiaTT, we will apply only minimal restrictions on participation because of acute, uncontrolled conditions and adapt the exercise programs based on individual baseline exercise capacity, comorbidities and disabilities, such as amputations. The intensity, duration, repetitions and/or load of exercises will be gradually increased. In addition to regular dialysis staff, exercise therapists will be present during the exercise sessions. Adverse events that are possibly related to exercise (hypotensive episodes, leg cramping, disconnection/dislodging of catheters/dialysis needles) and hospitalizations/deaths (SAEs) will be recorded to analyze safety of intradialytic training compared to UC [11].

### 4.4. Health Economics 

Assessments of health economics are essential for the future implementation of an intradialytic exercise program into clinical routine. Cardiac rehabilitation after coronary artery bypass grafting in HD patients (analysis between 1998–2004; n = 4324 patients, 36 exercise sessions in 12 weeks, follow-up period 42 months) revealed a cost-effectiveness ratio of $13,887 per year of life saved at 42 months [34]. Currently, however, there is no evidence from large trials regarding the cost-effectiveness of intradialytic exercise interventions in HD patients. Therefore, by including a detailed cost analysis, DiaTT will substantially improve the scientific and economic evidence base in order to inform future implementation strategies, as has been demanded by experts in the field [5,10,11].

## 5. Conclusions

The syndrome of CKD, together with the treatment-related immobility associated to in-center HD, results in low cardiorespiratory fitness and very low physical activity levels for many patients on HD. Although small- and medium-sized trials have shown the benefits of exercise, evidence of the effectiveness of exercise programs that are suitable for a broad range of patients from large-scale trials is lacking. The DiaTT trial will be the largest cluster randomized, controlled trial assessing the efficacy of intradialytic training for CKD patients on HD. By testing an exercise program that is embedded in routine dialysis care without interfering with other care processes, it will have broad applicability in many settings of dialysis care. Thereby, the DiaTT trial will substantially contribute to the current understanding of exercise for CKD patients during HD; and it has the potential to change recommendations and guidelines and to improve physical and mental wellbeing for these patients. 

## Figures and Tables

**Figure 1 mps-04-00060-f001:**
[figure not shown]
Study design of the DiaTT trial, including study visits (V). * From all the KfH dialysis centers in five regions in Germany, 28 will be recruited. ** In these centers, patients will be screened for eligibility (inclusion/exclusion criteria, informed consent) and included in the study (V0 screening). *** Centers will be randomized (1:1) to Intervention Group and Control Group. Visits will be at baseline (V1) and after 3, 6, 9 and 12 months (V2–V5).

**Table 1 mps-04-00060-t001:** Visits and examinations during the DiaTT trial.

	Screening Visit 0	Baseline Visit 1	Visit 2	Visit 3	Visit 4	Visit 5
**Month (+/−2 weeks)**	−2	0	3	6	9	12
Informed consent	X					
Inclusion and exclusion criteria	X					
Randomization	X					
Physician’s confirmation	X					
Medical history	X	X				
Laboratory test (blood sampling)		X	X	X	X	X
Medication		X	X	X	X	X
Dialysis parameters		X	X	X	X	X
SAE/AE		X				
**Physical functioning tests**						
STS60		X	X	X	X	X
TUG		X	X	X	X	X
6MWT		X	X	X	X	X
GST		X	X	X	X	X
Ergometry ^#^				X		X
Weekly training sessions		X	X	X	X	X
**Health literacy questionnaire**						
HLS-EU-Q16		X				X
**Quality of Life/ Frailty questionnaire**						
SF-36		X	X	X		X
MPI		X	X	X		X
**Health economics (costs)**						
Medication		X				X
Hospitalisation		X				X
Mode of transportation		X				X
Therapeutic remedies		X				X
Medical assistance tools		X				X
Nursing		X				X
Sick leave from work-place		X				X

SAE: serious adverse event; AE: adverse event; STS60: Sit-To-Stand test; TUG: Timed-Up-and-Go test; 6MWT: Six-Minute Walk test; GST: Grip Strength Test; HLS-EU-Q16 health literacy survey; SF-36: short form 36; MPI: Multidimensional Prognostic Index; ^#^ only Intervention Group (IG).
